### Assessments

We will conduct a total of three assessments. The first will be the baseline assessment (t0) before the randomization and the start of the intervention. The second and primary outcome will be three months after the randomization and the start of the intervention (t1) and the third will be after six months when the intervention is completed (t2) (see Table 2). All assessments will be conducted as self-reports via online-questionnaires, using a secure and widely used external online survey collection service (www.surveymonkey.com). The links to the questionnaires will be e-mailed to the participants.

**Table 2 Tab2:** Measures and measurement points

	AUDIT-C	QFI^1^	TFB^2^	Being Drunk^3^	Binge Drinking^3^	CAEQ^4^	AASE-G^5^	RCQ-G^6^	Readiness-Ruler^7^	ZUF-8^8,9^
Screening	X	X								
t0 baseline		X	X	X	X	X	X	X	X	
t1 three month follow-up		X	X	X	X	X	X	X	X	X
t2 six month follow-up		X	X	X	X	X	X	X	X	X

^1^Quantity- Frequency-Index (amount of alcohol in g) last 30 days, ^2^Timeline-Follow-Back (amount of alcohol in g) last 7 days, ^3^Single item, ^4^ The Comprehensive Alcohol Expectancy Questionnaire, ^5^Alcohol Abstinence Self-efficacy Questionnaire, ^6^Readiness to change Questionnaire, Readiness-Ruler, ^8^Patient satisfaction questionnaire, ^9^Intervention group only

### Primary outcome measures

***Measurement of alcohol consumption*** will be the *Quantity*- *Frequency*-*Index* (*QFI*) [40–42] and the *Timeline*-*Follow*-*Back* (*TFB*) method (amount of alcohol in gram) last 7 days. For the QFI the frequency of consumption and quantity of consumption per drinking day within the last 30 days will be measured. Based on beverage-specific alcohol content (beer, wine/sparkling wine, spirits and mixed drinks) the content of pure alcohol in gram will calculated [43]. With the TFB method the respondents are asked to recall their alcohol consumption within the past seven days. Both methods are described with advantages and disadvantages, e.g. in the QFI method respondents are likely to underestimate their drinking whereas the TFB approach does not capture the drinking behavior of infrequent drinkers [41]. For this reason both approaches will be combined in this study.

### Secondary outcome measures

***Drinking behavior*** will be assessed by one item asking for drunkenness (on how many days within the past 30 days did you feel drunk (e.g. unsteady on the feet, blurred vision)?) and one item asking for binge drinking (on how many days did you drink more than five drinks one occasion?). These items were based on the questions developed for the project “Standardizing Measurement of Alcohol-Related Troubles” (SMART) [44].

***Expectancies of effects of alcohol use*** will be measured with the short form of the "Comprehensive Alcohol Expectancy Questionnaire" (CAEQ) [45], a self-assessment instrument with 19 items asking for the expectation of effects of alcohol in terms of (a) social Assertiveness and positive affect (b) tension reduction (c) cognitive impairment and physical discomfort (d) aggression, and (e) sexual enhancement. Items can be rated on a 5-point Likert-scale ranging from 1 (not at all) to 5 (definitely). The CAEQ has been found as a psychometrically sound tool.

***Abstinence and relapse*** will be assessed with the *Alcohol abstinence self-efficacy scale - German Version (AASE-G)* the German version of the alcohol abstinence self-efficacy questionnaire contains two scales similar to the original English version [46]. The scales confidence and temptation, each consisting of the same 20 items that can be rated on a 5-point Likert scale. The items capture the temptation to drink in a given situation and the confidence not to drink in this situation. The instrument measures self-efficacy expectations of being able to withstand drinking alcohol, as well as self-perceived risk. For the AASE solid subscale structure and strong indices of reliability and validity were demonstrated.

***Self-efficacy and motivation to change*** is captured with two measures.

First, the *Readiness to Change Questionnaire* – German version (RCQ-G) the German translation of "Readiness to Change Questionnaire" [47, 48] will be used. The RCQ-G consist of 12-items on a 5-point rating scale ranged from to “strongly disagree” (−2) to “strongly agree” (+2). The self-assessment on the RCQ-G allocates persons to three stages of readiness to change (pre-contemplation, contemplation, action). The RCQ-G shows satisfying psychometric properties in a German population of high-risk drinkers behavior [48].

Second, the adapted German version of the Readiness-Ruler form Demmel (2005) [47, 49] will be applied. Participants will be instructed to rate two items on an 11-point Likert scale. 1) on the *importance ruler* they will be ask to rate how important it is to them to change their alcohol drinking behavior, 2) on the *confidence ruler* they estimate how confident they are about changing their behavior. Both scales range from 0 (=not important at all/not confident at all) to 10 (=very important/very confident).

**Satisfaction** with the intervention is captured with the *Patient satisfaction questionnaire (ZUF-8)* which has been tested as an economical and reliable instrument [50, 51] that assessed satisfaction with inpatient treatment. It consists of 8 items with four options to answer. The measure was adapted to assess the satisfaction with an Internet intervention.

***Additionally,*** key demographic data (e.g. sex, age, employment status) will be assessed including information about the use of other treatment options (e.g. outpatient/inpatient counseling, psychiatrist, psychologist, self-help group)*.* Furthermore, we will inquire about the first time of alcohol consumption and the start of regular use of alcohol [40].

### Statistical analysis

Descriptive statistics will be calculated for demographic data and the primary and secondary outcomes by treatment allocation.

To test the effectiveness of the web-based self-help program *Vorvida* the primary outcome will be the reduction in alcohol consumption of the *Vorvida* group compared to the CAU/WL control group. Therefore, a baseline adjusted linear-mixed model will be calculated to measure the change in alcohol consumption from the baseline to the follow-up measure. The group will be defined as fixed factor using the baseline variable as control.

The intention-to-treat (ITT) analysis of primary data will be based on all available data from all randomized participants. For the primary outcome, an analysis of covariance (ANCOVA) will be calculated for the difference between the intervention and control group at t1 with group and baseline values as fixed effects. An additional analysis will be conducted on a per-protocol analysis set. However, sensitivity analyses will be performed with different methods of missing value imputation to study the robustness of the findings. Only the result of this primary effectiveness efficacy analysis will be interpreted in a confirmatory manner.

The secondary outcomes will be analysed using a baseline adjusted linear mixed model with group and particular baseline values as fixed effects and time as repeated effect. Therefore, on the lowest hierarchical level autocorrelation and heteroscedasticity will be assumed.

The two-sided α-level will be set at 0.05.

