### Sample size

The sample size is estimated using Gpower v.3.0.5 software [32]. The calculation is based on the primary outcome measure (alcohol consumption).

Other studies on Internet self-help programs on alcohol misuse showed mainly small effect sizes between d > .2 and d < 0.4 [11, 18].

To detect effect sizes of d = 0.28, an effect derived from a meta-analysis of self-guided Internet interventions [18], with a power of 0.80 and a significance level of 0.05 to compare the *Vorvida* group with the CAU/WL group, a target sample size of N = 404 (n = 202 per group) is required. Since it is expected that 20 % of variance can be explained through baseline-covariance, adjusted effect sizes were used in this power calculation.

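### The primary three-month ANCOVA is valid but names only group and baseline values; adding screening QFI, sex and, if not already in, the second consumption measure would give a small precision gain at almost no cost

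*Protocol article*

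**What the plan says.** All references are to the protocol article; no separate SAP is shown.

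- **Primary model (Statistical analysis).** The confirmatory comparison is an ANCOVA "at t1 with group and baseline values as fixed effects". The paragraph before it, which describes a mixed model, says: "The group will be defined as fixed factor using the baseline variable as control". No other covariate is named in either place.
- **Readings taken (Assessments, Table 2, titled "Measures and measurement points").** QFI, with a 30-day window, is marked at screening and again at t0. TFB, with a 7-day window, is marked at t0.
- **Order of events (Study procedure; Randomization).** Screening comes first, then the t0 questionnaire, then randomisation.
- **Sex.** Under Secondary outcome measures, "key demographic data (e.g. sex, age, employment status) will be assessed", without a time point. The gram limit for entry differs by sex (24/12 g, Inclusion and exclusion criteria), so sex has to be known at screening.
- **Expected value of baseline (Sample size).** The plan expects 20% "of variance can be explained through baseline-covariance".

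**The concern.** A single self-report over 30 or 7 days is a noisy reading of usual drinking. A second reading taken before randomisation can average out part of that noise, and sex may add something too. Covariates measured before randomisation and fixed in advance leave the group comparison unbiased, and any that predict the outcome narrow its confidence interval. The article collects such variables but does not say that the confirmatory model will use them.

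The stake is precision in the one analysis that is to be read as confirmatory. The planned 404 is exactly the number that the power calculation needs, so there is no visible reserve. The same variables could also make a missing-at-random assumption more credible where t1 responses are lost, but only if they relate to the outcome and to the loss. The article does not show that they do.

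**Working it through.** **Inputs.** From Sample size: "To detect effect sizes of d = 0.28, an effect derived from a meta-analysis of self-guided Internet interventions", "with a power of 0.80 and a significance level of 0.05", N = 404 (202 per group), and 20% of variance explained by baseline. From Statistical analysis: "The two-sided α-level will be set at 0.05". The correlations between readings are not in the article; I assume a range.

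**Step 1: reproduce the plan's N.** For two means with standardised difference d, the normal approximation is n per arm = 2(1.960 + 0.842)²/d². With d = 0.28 this is 2 × 7.85/0.0784 = 200.2, so 201. The exact noncentral-t calculation gives 202 per arm, N = 404, power 0.802. The plan's figure is reproduced with 0.28 entered as it stands. Applying the 20% on top (d = 0.28/√0.80 = 0.313) gives 162 per arm, N = 324, which does not match. I therefore take 0.28 as already adjusted, as the section says. The unadjusted effect is then 0.28 × √0.80 = 0.250.

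**Step 2: variance explained by more than one reading.** Assume that each of k readings alone explains 20% of the variance of the t1 outcome and that any two readings correlate at r. Then

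R² = 0.20k/[1 + (k − 1)r].

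For k = 2 this is 0.40/(1 + r); for k = 3 it is 0.60/(1 + 2r). The residual variance relative to the plan is (1 − R²)/0.80. The adjusted effect is 0.250/√(1 − R²), and power is the exact t value at 202 per arm. The equivalent extra sample is 404/ratio − 404.

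| Readings in the model | r | R² | Fall in residual variance | Adjusted d | Power | Equivalent extra participants |
|---|---|---|---|---|---|---|
| One (plan) | – | 0.200 | – | 0.280 | 0.802 | – |
| t0 and screening QFI | 0.7 | 0.235 | 4.4% | 0.286 | 0.819 | 19 |
| t0 and screening QFI | 0.9 | 0.211 | 1.3% | 0.282 | 0.807 | 5 |
| Both QFI and t0 TFB | 0.7 | 0.250 | 6.3% | 0.289 | 0.826 | 27 |
| Both QFI and t0 TFB | 0.9 | 0.214 | 1.8% | 0.283 | 0.809 | 7 |

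The confidence interval narrows with the square root of the variance ratio: by about 0.7% at the smallest gain (1 − √0.987) and 3.2% at the largest (1 − √0.9375).

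**Step 3: the other reading of 0.28.** If 0.28 is the unadjusted effect, power with one baseline is already 0.881. It rises to 0.885 (two readings, r = 0.9) up to 0.900 (three readings, r = 0.7). The direction is the same and the size similar.

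**Step 4: where in the range?** Under Study procedure, the eligibility e-mail comes within one week of screening and t0 is requested within one further week. If t0 follows screening by at most 14 days, the two 30-day QFI windows share at least 30 − 14 = 16 days, or 53%. Late responders overlap less. The 7-day TFB window at t0 lies inside the t0 QFI window. High r is therefore plausible. Consumption at screening is also an entry criterion, and selection on it tends to restrict the range of screening QFI and weaken it as a predictor. Both point to the lower end.

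**Step 5: the cost if the covariates turn out useless.** In a simulation of 4,000 trials at 202 per arm, adding three covariates unrelated to the outcome moved power from 0.803 to 0.798, within simulation error (standard error about 0.006).

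**The case against.** The strongest reply is that nothing here is an error. The ANCOVA is pre-specified and baseline-adjusted, and a condensed article may leave further covariates and the imputation variables to a fuller document. The first part stands: a reader might infer that the planned test is biased or invalid, and the article does not support that. The second part stands for the imputation models, where the article already promises sensitivity analyses under several methods. It carries less weight for the primary model, because the article itself states that model's covariates.

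Four further objections limit the size of the point:

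- **TFB may already be in the model.** A reader might infer that the only covariate is the t0 value of one measure. The ANCOVA sentence uses the plural, and Primary outcome measures says that QFI and TFB are to be combined without saying how. If the outcome is a composite, or both baselines enter, t0 TFB is already used. Screening QFI and sex remain unnamed either way.
- **The 20% is not stated per reading.** Giving each reading its own 20% is my assumption. If 20% is the joint contribution of several baseline readings, the table overstates the gain over planned power.
- **Sex.** A reader might infer from the sex-specific entry limit that sex must be prognostic. The limit shows that sex is known before randomisation, not that it predicts t1 grams once baseline grams are in the model.
- **Not wholly free.** With 340 participants recruited at the time of writing (Trial status), changing a published confirmatory model needs a documented amendment.

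None of these reverses the direction of the gain or shows a material cost.

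**Conclusion.** The point holds as a small, nearly costless improvement. The primary analysis is valid as it stands. Under the assumptions of equal predictive value (20% each) and correlations of 0.7 to 0.9 between readings, the extra consumption readings reduce residual variance by about 1 to 6% and raise power from 0.80 to about 0.81 to 0.83 at 202 per arm. A gain of about one power point is more likely than two or three. No figure can be put on sex. The article does not support a claim that the trial loses much power through this choice. The case for acting is that the variables are already collected and the possible loss is negligible.

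**What to change.** Before unblinding, replace the covariate wording of the primary analysis with an explicit list, all measured before randomisation:

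t1 outcome ~ group + t0 value of the same measure + screening QFI + sex, plus the t0 value of the other consumption measure if it is not already part of the analysed outcome.

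Use the same variables in the imputation models for the sensitivity analyses, and report the model with the single same-measure baseline as a check. The list would also settle which baseline values the ANCOVA sentence means.

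The cost is up to three degrees of freedom out of about 400 and a dated, documented change to the analysis text. No new data, questionnaires or participants are needed.

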**Methods/Design:**

A two-arm randomized control trial (RCT) will be conducted to determine whether using Vorvida results in greater reductions in self-reported problem drinking, compared with a care-as-usual/waitlist (CAU/WL) control group. There will be a baseline assessment (t0) and follow-up assessments after three (t1) and six months (t2). Inclusion criteria will be: minimum age of 18, an average consumption of alcohol >24/12 g (men/women) per day and an AUDIT-C score ≥ 3, as well as informed consent. Participants will be randomly assigned to the intervention or control condition at a ratio of 1:1. Recruitment, informed consent, randomization and assessment will be Internet-based. Primary outcome will be change in self-reported alcohol consumption between t0 and t1. Secondary outcomes will be self-reported drinking behavior, expectancies of effects of alcohol use, abstinence and relapse tendencies, self-efficacy and motivation to change.

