In addition, many interventions described in these meta-analysis [11, 16, 22, 23] can be accessed via Internet but are severely limited in the extent to which they use the interactivity and tailoring opportunities afforded by current software technology. Essentially, some Internet interventions consist of little more than conventional self-help text, offered in the same format to all users, without few or no interactive or “responsive” program features or custom-tailoring of content [24]. Programs that use many interactive elements, tailoring of content, and responsive web-design (i.e., self-adjusting layout of a program to the characteristics of the device used, such as desktop, tablet, smartphone), should allow for more flexible use and more user engagement, which in turn might enhance the effectiveness of the intervention. Indeed, meta-analyses have shown that interactive or tailored interventions tend to outperform non-tailored interventions in trials seeking to improve health-related knowledge or change health-related attitudes and behavior [24]. “Computer-tailoring” is a technique of adaptive communication which is described as a “combination of strategies and information intended to reach one specific person based on characteristics that are unique to that person, related to the outcome of interest, and derived from an individual assessment” [25]. Some Internet interventions use this tailoring principle by continuously requesting individual user choices and then adjusting subsequent content, in a manner that simulates an individual “dialogue” between user and the program [26, 27].

The purpose of this study is to test the effectiveness of *Vorvida*, a responsive and tailored Internet intervention against a care as usual (CAU)/waitlist (WL) condition. First, we hypothesize participants in the intervention condition, compared to the control group, will report significantly greater reductions in alcohol consumption at the three month (t1) and six month time-points (t2) compared to CAU, with t1 considered to be the time-point of primary interest. Second, we hypothesize that participants receiving the intervention differ from those in the CAU condition in measures of expectancies of effects of alcohol use, abstinence and relapse, self-efficacy and motivation to change.

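### The plan forgoes a confirmatory six-month (t2) claim on alcohol consumption that a t1-then-t2 fixed sequence would allow without extra patients, t1 alpha or t1 power (optional improvement, not an error)

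*Protocol article*

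**What the plan says.** The Background of the protocol article states the first hypothesis for two time points. Participants given the program "will report significantly greater reductions in alcohol consumption at the three month (t1) and six month time-points (t2) compared to CAU", and the same sentence ends by ranking them, "with t1 considered to be the time-point of primary interest". The abstract follows that ranking: "Primary outcome will be change in self-reported alcohol consumption between t0 and t1".

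The Statistical analysis section specifies for the primary outcome an ANCOVA that "will be calculated for the difference between the intervention and control group at t1 with group and baseline values as fixed effects". It then limits the claim: "Only the result of this primary effectiveness efficacy analysis will be interpreted in a confirmatory manner". It adds: "The two-sided α-level will be set at 0.05".

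The Sample size section plans 404 participants, 202 per group, to detect d = 0.28 "with a power of 0.80 and a significance level of 0.05". Under Study design, controls receive access after completing the t2 questionnaires.

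**The concern.** The hypothesis predicts a significant difference at t2 as well as t1, while the testing rule gives t2 no route to confirmatory status. The word that opens the restriction, only, is an explicit rule, not a detail left to a later document. An analysis plan that added a confirmatory t2 step would contradict the published text.

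The stake is what the trial may conclude about persistence. The program is active for 180 days, so t1 falls about halfway through access. The Assessments section describes t2 as the point when the intervention is completed. It is also the last comparison in which the control group has not been offered the program. Under the present rule a clear six-month difference can be estimated and reported, but not claimed as confirmed.

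**Working it through.** **1. The plan's own figure.** Inputs from the Sample size and Statistical analysis sections: d = 0.28, power 0.80, two-sided alpha 0.05, 1:1 allocation.

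Normal approximation: n per arm = 2(1.960 + 0.842)² / 0.28² = 200.2, rounded up to 201. The two-sample t-test version gives 201.2, rounded up to 202, so N = 404 as stated. The match requires 0.28 to be the effect size entered directly. Taking a further 20% off the variance for the baseline covariate would give about 161 per arm. The steps below therefore use 0.28 as entered.

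Power at t1 with 202 per arm: the mean of the test statistic is 0.28 × √(202/2) = 2.814, and Φ(2.814 − 1.960) = 0.803.

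**2. Error rate of the present plan.** One confirmatory test at two-sided 0.05 gives an error rate of 0.05. Nothing needs repair here.

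**3. Error rate of a fixed sequence.** Test t1 at 0.05, and t2 at 0.05 only if t1 is significant.
- No effect at either time: a false claim requires t1 to reject, so the error is 0.05.
- Effect at t1 (d = 0.28), none at t2: a false claim requires both to reject, which cannot exceed 0.05. For assumed correlations of 0.3 to 0.9 it is 0.038 down to 0.025.
- The t1 test is the one already planned, so its alpha, its power and N do not change.

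**4. Chance of confirming both time points.** P(|Z₁| > 1.96 and |Z₂| > 1.96), where Z₁ and Z₂ are bivariate normal with unit variances, means d₁√(n/2) and d₂√(n/2), and correlation r. The documents give neither r nor a t2 effect nor an attrition rate. Assumed: r = 0.4, 0.6, 0.8; d₂ = 0.28 or 0.20; loss of 0, 20% or 40% in each arm at both times (202 × 0.8 = 162; 202 × 0.6 = 121).

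| Analysed per arm | Mean of Z₁ (d = 0.28) | Mean of Z₂ (d₂ = 0.20) | Power at t1 | Both, d₂ = 0.28 (r = 0.4 / 0.6 / 0.8) | Both, d₂ = 0.20 (r = 0.4 / 0.6 / 0.8) |
|---|---|---|---|---|---|
| 202 | 2.814 | 2.010 | 0.80 | 0.68 / 0.70 / 0.73 | 0.46 / 0.49 / 0.51 |
| 162 | 2.520 | 1.800 | 0.71 | 0.56 / 0.59 / 0.63 | 0.36 / 0.39 / 0.42 |
| 121 | 2.178 | 1.556 | 0.59 | 0.41 / 0.44 / 0.49 | 0.26 / 0.29 / 0.32 |

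The fall in t1 power with attrition is the same with or without the second step.

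**5. The precondition.** The result in step 3 needs exactly one test at t1. The section on primary outcome measures lists two, the Quantity-Frequency-Index (QFI) over 30 days and the Timeline-Follow-Back (TFB) over 7 days. It says they will be combined but not how. The Statistical analysis section describes both a baseline-adjusted mixed model and an ANCOVA for the primary outcome. If success on either measure at t1 counted, each tested at 0.05, the first step alone would have an error rate of 0.091 to 0.071 for assumed correlations of 0.5 to 0.9.

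**The case against.** The strongest reply is that nothing here is wrong. The hypothesis sentence itself puts t1 first. The abstract, the Assessments section and the ANCOVA all place the primary outcome at three months. Predicting an effect at a subordinate time point does not oblige a trial to test it confirmatorily, and a single confirmatory test is a common and conservative choice. The t2 data are still collected and can be reported with an estimate and confidence interval. All of this stands.

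Two stronger readings are tempting. A reader might infer that half of the main hypothesis contradicts the testing rule. The documents do not support that, because t2 is openly ranked below t1 and the sections agree with each other. A reader might also infer an inflated error rate. Testing both time points at 0.05 and counting either as success would give a familywise error of 0.078 to 0.093 for correlations of 0.8 to 0.4. The confirmatory restriction already excludes that practice, so the figure does not describe this plan.

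The reply is also right that a sequence is free of alpha cost only once a single t1 test is defined, and that probabilities based on 202 per arm are best cases. The Discussion expects high attrition in Internet studies without giving a rate. What the reply does not remove is that a confirmatory six-month claim is available and is not taken up.

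**Conclusion.** This is a low-severity improvement. The plan is coherent, and its single confirmatory test controls the error rate at 0.05. It gives up a confirmatory t2 claim that it could have at no cost in sample size, t1 alpha or t1 power.

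With 202 per arm analysed, the chance of confirming both time points is 0.68 to 0.73 if d is 0.28 at t2, and 0.46 to 0.51 if it is 0.20. With 20% attrition these become 0.56 to 0.63 and 0.36 to 0.42. With 40% they become 0.41 to 0.49 and 0.26 to 0.32. The correlation (0.4 to 0.8), the t2 effects and the attrition rates are assumptions. The conclusion that t1 alpha, t1 power and N are unchanged does not depend on them, but it does depend on there being one uniquely defined t1 test.

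**What to change.** Before any unblinded look at the data, replace the confirmatory sentence with wording such as:

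*The single primary test is the baseline-adjusted ANCOVA of the group difference at t1 on [one named consumption measure, or one pre-defined combination of QFI and TFB], at two-sided 0.05. If and only if it is significant, the group difference at t2 on the same measure, with the same baseline adjustment, is tested at two-sided 0.05. Both tests are confirmatory in this order. All other outcomes are exploratory.*

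If the sponsor prefers to keep one confirmatory test, it is enough to state in the first hypothesis that t2 is exploratory.

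The cost is a few lines in the protocol and analysis plan, plus the choice of one measure and one model, which the t1 test needs in any case. No extra data or participants are required. The only restriction is that t2 cannot be claimed if t1 fails, which is no worse than the present rule.

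### Hypothesis 1 claims an effect on consumption at both t1 and t2, but the models as written estimate a visit-specific effect only at t1 and average the secondary outcomes over the two visits

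*Protocol article*

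**What the plan says.** Background, hypotheses: participants in the intervention arm "will report significantly greater reductions in alcohol consumption at the three month (t1) and six month time-points (t2) compared to CAU", with t1 named as the time-point of primary interest. Hypothesis 2, on expectancies, abstinence and relapse, self-efficacy and motivation, says only that the arms differ and names no time-point.

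The Statistical analysis section then sets out three models:

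- **Mixed model for consumption**, for change from baseline to follow-up (in the singular): "The group will be defined as fixed factor using the baseline variable as control". No time or interaction term is named.
- **ANCOVA for the primary outcome**: "an analysis of covariance (ANCOVA) will be calculated for the difference between the intervention and control group at t1". Only this primary analysis is to be read as confirmatory.
- **Mixed model for the secondary outcomes**: a "baseline adjusted linear mixed model with group and particular baseline values as fixed effects and time as repeated effect". The next sentence adds that "on the lowest hierarchical level autocorrelation and heteroscedasticity will be assumed".

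Table 2 in Assessments shows the consumption measures and the secondary outcomes collected at both t1 and t2.

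**The concern.** A repeated effect describes how residuals from the same person vary and correlate across visits. It puts no time term in the mean. With group and baseline as the only fixed effects, the model has a single group coefficient, which must stand for both visits. It cannot show whether an effect seen at three months is still there at six.

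For consumption this leaves half of hypothesis 1 without a matching estimate. That half matters. By Study design, the control arm receives access after the t2 questionnaires, so t2 is the last comparison between the arms as randomized. It is also the visit at which the intervention is described as completed. For the secondary outcomes, two visits per person would be reduced to one number, and an effect that fades or grows would be reported as constant.

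There is a second, smaller issue. Without a time main effect, any common shift in means between t1 and t2 that coincides with unequal t2 dropout enters the group coefficient. The Discussion itself warns that attrition is often high in Internet trials.

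**Working it through.** **1. Hypotheses against models.**

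- Consumption at t1 (hypothesis 1, primary): estimated by the ANCOVA.
- Consumption at t2 (hypothesis 1): the ANCOVA is at t1 only. The consumption mixed model names group and baseline only. The third model is assigned to the secondary outcomes. No stated analysis yields this contrast.
- Secondary outcomes (hypothesis 2, no time-point): one group coefficient from the third model.

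**2. Plan's figure used below.** Sample size gives 202 per group for d = 0.28, power 0.80, two-sided 0.05. A two-sample t-test needs 201.2 per arm, rounded up to 202, so N = 404 reproduces. This point disputes no figure; 202 per arm only sets the size of the illustrations.

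**3. What the single group coefficient estimates.** Let d1 and d2 be the true effects at t1 and t2 (as sizes of reduction), s1 and s2 the residual SDs, and r the residual correlation. With complete data, generalized least squares gives

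coefficient = w1·d1 + (1 − w1)·d2, where w1 = (s2² − r·s1·s2) / (s1² + s2² − 2r·s1·s2).

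With equal SDs, w1 = 1/2. The effects, SDs and r = 0.6 are assumptions, except that 0.28 is borrowed from the sample size section. The simulations used 202 per arm, 400 runs and baseline R² of about 0.2.

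- d1 = 0.28, d2 = 0.14, equal SDs: (0.28 + 0.14)/2 = 0.21. Read as a t1 effect, that is 0.21/0.28 = 0.75 of the truth. Read as a t2 effect, it is 0.21/0.14 = 1.50 times the truth.
- d1 = 0.28, d2 = 0.10, SDs 0.9: (0.28 + 0.10)/2 = 0.19. Simulated: 0.186 as written, 0.186 with time added alone, and 0.273 (t1) and 0.099 (t2) with time and group-by-time.
- d1 = 0.28, d2 = 0, SDs 0.8 and 1.0: w1 = (1.00 − 0.48)/(0.64 + 1.00 − 0.96) = 0.52/0.68 = 0.765, and 0.765 × 0.28 = 0.214. Simulated: 0.215 as written, and 0.283 and 0.00 with the interaction.
- d1 = d2 = 0.28: every version returns 0.28.

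The group-by-time term is what separates the visits. A time main effect alone does not.

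**4. Bias from unequal t2 dropout.** Assume no true effect, complete t1 data, purely random dropout at t2, equal variances, r = 0.6 and a common mean shift D from t1 to t2. In an arm with share p observed at t2, the fitted mean moves from the t1 mean by D·k(p), where

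k(p) = [p/(1 + r)] / [2p/(1 + r) + 1 − p].

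This gives k(0.9) = 0.459, k(0.8) = 0.417, k(0.7) = 0.372, k(0.6) = 0.326 and k(0.5) = 0.278. The spurious group coefficient has size |D| × the difference in k:

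- D = 0.2 SD, 80% v 70% observed: 0.2 × 0.044 = 0.009 SD
- D = 0.2 SD, 80% v 50%: 0.2 × 0.139 = 0.03 SD
- D = 0.3 SD, 80% v 60%: 0.3 × 0.091 = 0.03 SD
- D = 0.3 SD, 90% v 50%: 0.3 × 0.181 = 0.05 SD

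Its sign depends on which arm loses more participants and on the direction of the shift. A time main effect removes it in these scenarios.

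**5. Price of visit-specific estimates.** With equal variances and complete data, the standard error of a one-visit contrast divided by that of the averaged one is √(2/(1 + r)). At r = 0.6 this is √1.25 = 1.118, so intervals are about 12% wider.

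**The case against.** The strongest reply is that the visit-specific wording and the averaging model belong to different outcomes. The model with time as a repeated effect is introduced by "The secondary outcomes will be analysed using a baseline adjusted linear mixed model", while the t1 and t2 claim is about consumption. Hypothesis 2 names no time-point, so a visit-averaged difference answers it as worded. This stands, and it limits the point to the t2 effect on consumption and to the information lost on the secondary outcomes.

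A reader might infer that the primary result is diluted. The documents do not support that: t1 consumption has its own ANCOVA, the only confirmatory test, and its estimate does not pass through the averaging model. The 0.21 against 0.28 shows what averaging does. It is not a bias in the primary analysis.

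A reader might also infer that the linear model is wrong for the RCQ-G because that instrument assigns people to three stages. The text also describes 12 items rated from −2 to +2 and does not say whether stage or score is analysed, so no error is established. Nor is there a case for demanding an unstructured covariance: with two follow-up visits, two variances and one correlation are already what the stated residual assumptions allow.

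Finally, this is a condensed article, and naming time as a repeated effect may be shorthand for a within-person factor with the usual fixed terms. A fuller analysis plan may say so. But the article does list the fixed effects, and the sentence after the model ties the lowest level to residual structure. The point is about a model as stated, not about silence. The planned descriptive statistics by arm could show fading, but without baseline adjustment.

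**Conclusion.** The point holds in a limited form. As written, no analysis estimates the t2 effect on consumption that hypothesis 1 states, and the secondary outcomes measured in both arms at t1 and t2 each get one visit-averaged group effect.

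The size depends on how far the two true effects differ, which the documents do not give. It is nil if they are equal; assumed effects of 0.28 and 0.14 would be reported as a single 0.21. The dropout bias from omitting the time main effect is secondary: about 0.01 to 0.05 SD under the assumptions shown, and zero if means do not shift between visits or dropout at t2 is equal between arms.

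Everything affected is non-confirmatory. The t1 ANCOVA, the sample size and the ability to answer hypothesis 2 as worded are untouched. The change is still worth making, because a pre-stated hypothesis lacks its estimate and the remedy is one sentence.

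**What to change.** In Statistical analysis, state the mixed model with group, time (t1, t2), group-by-time and the outcome's baseline value as fixed effects, and keep the residual structure already described. Report the group contrast at t1 and at t2, each with a 95% confidence interval. State that the same model is applied to consumption and supplies the t2 contrast for hypothesis 1 as a non-confirmatory analysis, with the t1 ANCOVA remaining the sole confirmatory test. A baseline-by-time term is optional.

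The cost is some precision: visit-specific intervals are somewhat wider than the averaged one, by about 12% under the assumed correlation of 0.6. If a single overall effect is also wanted for hypothesis 2, the mean of the two contrasts can be reported from the same fit. No new data, visits or participants are needed.
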